### Ethics and dissemination

2.13

This study was approved by the Ethics Committee of Hubei Provincial Hospital of TCM on 15 November 2018 (Ethics Reference No:HBZY2018-C24-01). This study was registered at https://register.clinicaltrials.gov/prs/app/action/SelectProtocol?sid=S000ACAK&selectaction=Edit&uid=U00034LN&ts=6&cx=luql35 (ClinicalTrials.govID,NCT04606680). Written informed consents will be provided by all participants before they were enrolled in this study. Their personal information will be collected, and maintained in an independent closet to protect confidentiality before, during, and after the clinical trial.

## Discussion

3

To ensure the quality of this randomized controlled trial, only participants who meet the inclusion criteria of simple obesity will be recruited. Moreover, participants will be excluded if they have endocrine disorders such as polycystic ovary syndrome, diabetes mellitus, or hypertension, or abnormal liver and kidney functions, or mental diseases. Medications related to these diseases may affect the clinical results by interacting with the planned interventions.

Obesity is a common metabolic and endocrine disease which seriously affects patients’ quality of life, and long-term physical and mental health.^[18]^ The clinical complications associated with this disease are complicated, and the interventions are highly heterogeneous. Different treatment methods also exist for the condition. Although conservative management of obesity which includes lifestyle modification and anti-obesity drugs can reduce body weight to some extent, it still has some limitations owing to considerable drug-related side effects (e.g., headache, dizziness, insomnia, constipation, and gastrointestinal adverse effects), poor compliance and possible weight regain once the treatment stops. The gastrointestinal surgery can greatly reduce excess weight, but only approximately 61.7% population reached the therapeutic goal of weight-loss for that the cost and the risk of postoperative complications are both high, and there are strict indications, which was unsatisfactory.^[18–20]^ Therefore, there is an urgent to seeking help from alternative interventions to treat these obese people who are unsuitable candidates for gastrointestinal surgery and also respond inadequately to conservative treatments.

In the past 50 years, it has been illustrated that obesity is mainly caused by a dysfunctional relationship between Spleen, Liver, Kidney, and the sanjiao (triple energizer), and its pathogenesis is closely related to the blood vessel obstruction by Qi deficiency and phlegm dampness stagnation, which might be caused by various internal and external factors such as stasis of liver Qi, deficiency of spleen, or over intake of greasy flavour. Based on the foundation of this theory, the therapeutic principle of simple obesity is invigorating spleen to remove dampness and relieving Qi stagnancy in Liver to remove blood stasis.^[21,22]^ We designed this clinical trial to evaluate the efficacy and safety of partitioned moxibustion plus lifestyle modification treatment for patients with simple obesity. The participants’ obesity-related indicators, the IWQOL-Lite scale, and the syndrome score of TCM. Adverse events will be recorded and reported.

Moxibustion also has been widely used in China for more than 2500 years. Herb-partitioned moxibustion is a critical component of moxibustion therapy in TCM. It treats diseases by placing a piece of herb formula on the patient's acupuncture points and then igniting a moxibustion tube on the herb formula. While to be different with the traditional partitioned moxibustion, herb-partitioned moxibustion used in this study can not only produce heat stimulation and infrared radiation necessary for moxibustion, but also effectively avoid smoke pollution and open fire danger, and can also play the role of medicine. Therefore, we considered whether this new type of herb-partitioned moxibustion therapy could be more effective in improving related symptoms in patients with simple obesity. There is a lack of relevant clinical evidence in this regard, which we aim to address in this clinical trial. Thus, we will provide supporting evidence for this new type of herb-partitioned moxibustion therapy to treat simple obesity. However, this protocol still has some limitations. Firstly, because of the limited funding and the lack of adequate preliminary studies, this survey has been designed as a single-center pilot study with a small sample size. Secondly, although all outcomes will be measured and recorded by an independent researcher in order to minimize the risk of detection bias, the double-blind procedure cannot be completely adopted for the acupuncture therapist. Nevertheless, we expect that this randomized controlled trial will be able to provide some new evidence regarding this modern new herb-partitioned moxibustion therapy in the treatment of simple obesity.

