To date, there are no studies on the effect of a combined application of herb-partitioned moxibustion plus lifestyle modification treatment in patients with simple obesity. We will conduct a 3-arm parallel clinical trial. In this study, our aim is to investigate the effects of a combined application of herb-partitioned moxibustion plus lifestyle modification treatment in terms of obesity-related indicators, the syndrome score of TCM, and the improvement of the quality of life in patients with simple obesity. We hypothesize that a combination of partitioned moxibustion plus lifestyle modification treatment will produce more beneficial results than the application of these therapies alone in addressing obesity symptoms.

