### Sample size calculation

2.11

In a previous study, the effective rate of simple obesity in the herb-partitioned moxibustion group was *P*1 = .80. The effective rate of the heat application group was *P*2 = .65, and the effective rate of the medicated plaster group was *P*3 = .6. PASS V.11 software (NCSS, Kaysville, UT) was used to calculate that, based on 80% power to detect a significant difference(α = 0.025, 1 sided), 33 participants will be required for each group. Allowing for a 10% withdrawal rate, we plan to include a total of 108 participants with 36 participants in each group.

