### Statistical analysis

2.12

The data of all participants will be conducted in the final statistical analysis which will be in accordance with the per-protocol principle and the intent-to-treat principle. The data statisticians will be blinded to the group allocation. The SPSS software v19.0 (Statistics 19.0, SPSS, IBM Corp., Chicago, IL) will be used for statistical processing. Measurement data will be presented in the form of mean ± standard deviation, while count data will be expressed as percentage and number. The continuous variables, such as participants’ obesity-related indicators including weight, BMI (weight/height), body fat percentage, basic metabolism value, WC, HC, waist-to-hip ratio (WC/HC), visceral fat area, body fat, and obesity degree will be presented as mean ± SD. Between-group comparisons will be performed by ANOVA or its non-parametric equivalents on changes from baseline to after treatment. Intra-group comparison will be performed by using the Kruskal–Wallis test. All statistical tests will be performed on both sides, and the difference will be considered statistically significant when *P* < .05.

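### Section 2.11 claims 80% power from earlier rates while the Discussion calls the same sample a small pilot; the plan's own rates give about 27% to 46% power per comparison

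*Protocol article*

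**What the plan says.** **Sample size calculation (2.11).** The rates are attributed to earlier data: "In a previous study, the effective rate of simple obesity in the herb-partitioned moxibustion group was" 0.80, with 0.65 for heat application and 0.60 for medicated plaster. No citation is given. The calculation is "based on 80% power to detect a significant difference" at one-sided α = 0.025. It arrives at 33 per group, raised to 36 per group (108 in total) for 10% withdrawal.

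**Statistical analysis (2.12).** Tests are two-sided, and "the difference will be considered statistically significant when" P < .05.

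**Introduction (1).** "To date, there are no studies on the effect of a combined application of herb-partitioned moxibustion plus lifestyle modification treatment" in simple obesity. Section 2.7.1 prescribes diet and exercise to all participants, so every arm of this trial has that background.

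**Discussion (3).** The limitations paragraph says that "this survey has been designed as a single-center pilot study with a small sample size". It attributes this to limited funding and to preliminary studies that were not adequate. It also says that relevant clinical evidence on this new form of the therapy is lacking.

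**The concern.** The article explains one sample size in two ways. In 2.11 it is the output of a power calculation that takes arm-specific rates from earlier data. In the Discussion it is small because money and adequate earlier data were missing. The two accounts lead to different readings of the result. Under 80% power, a non-significant comparison would be fair evidence against a difference of the planned size. Under a pilot it would say little. A reader who relies on 2.11 would draw a conclusion from a null result that the trial cannot support.

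The source of the rates has the same difficulty. If the earlier study gave lifestyle modification, the Introduction's statement about prior work needs changing. If it did not, the three rates describe a different regimen from the one tested here, and 2.11 should say so.

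**Working it through.** **Inputs, all from 2.11.** Rates: herb-partitioned moxibustion p1 = 0.80, heat application p2 = 0.65, medicated plaster p3 = 0.60. One-sided α = 0.025 (z = 1.960, the same critical value as two-sided 0.05 in 2.12). Power 80% (z = 0.8416). n = 33 per arm, 36 enrolled.

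**Step 1. Try to reproduce 33 per group.** Pooled two-proportion formula, with p̄ the mean of the two rates:

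n = [1.960·√(2p̄(1−p̄)) + 0.8416·√(p1q1 + p2q2)]² / (p1 − p2)²

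- Against heat: p̄ = 0.725, so √0.39875 = 0.6315 and √0.3875 = 0.6225. n = (1.2377 + 0.5239)² / 0.15² = 3.103 / 0.0225 = 137.9, so **138**.
- Against plaster: p̄ = 0.70, so √0.42 = 0.6481 and √0.40 = 0.6325. n = (1.2702 + 0.5323)² / 0.20² = 3.249 / 0.04 = 81.2, so **82**.

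Other standard methods do not reach 33 either. The unpooled formula gives 136 and 79, the arcsine formula 137 and 81, and the continuity-corrected formula 151 and 91. A three-group chi-square test needs 97 per group at α = 0.05 or 115 at 0.025. Figures near 33 appear only with inputs that 2.11 does not state. For example, a one-sample test of 0.80 against 0.60 at one-sided 0.05 gives 33.

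**Step 2. Power that the sample provides.** Power = Φ{[(p1 − p2)√n − 1.960·√(2p̄(1−p̄))] / √(p1q1 + p2q2)}

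| Comparison | n = 33 per arm | n = 36 per arm |
|---|---|---|
| 0.80 v 0.65 | Φ[(0.8617 − 1.2377)/0.6225] = Φ(−0.604) = **27%** | Φ[(0.9000 − 1.2377)/0.6225] = Φ(−0.542) = **29%** |
| 0.80 v 0.60 | Φ[(1.1489 − 1.2702)/0.6325] = Φ(−0.192) = **42%** | Φ[(1.2000 − 1.2702)/0.6325] = Φ(−0.111) = **46%** |

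A three-group chi-square test at 0.05 has power of about 35% (33 per arm) or 38% (36 per arm).

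**Step 3. Expected 95% interval.** Half-width = 1.96·√[(p1q1 + p2q2)/n]

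- Against heat, n = 33: 1.96·√(0.3875/33) = 0.212. The interval is 15 points, **−6 to +36**.
- Against plaster, n = 33: 1.96·√(0.40/33) = 0.216. The interval is 20 points, **−2 to +42**.
- At n = 36 the half-widths are 0.203 and 0.207, giving −5 to +35 and −1 to +41.

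All four intervals include zero when the observed differences equal the assumed ones.

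**Step 4. Why a significant estimate would tend to be too large.** With 33 per arm and the pooled rates above, significance needs an observed difference of about 1.2377/√33 = 21.5 points against heat, where 15 is assumed. Against plaster it needs 1.2702/√33 = 22.1 points, where 20 is assumed. Only results above the assumed effect pass the threshold.

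**The case against.** The strongest reply is that this is loose wording in a limitations paragraph. Section 2.12 sets a general significance threshold and no trial-level rule for success, and the Discussion itself expects only some new evidence. That is fair as to tone. It does not repair 2.11, whose 80% figure does not follow from its own inputs.

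Three stronger readings might be inferred, and the documents support none of them.

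- *That P < .05 could not count as evidence of efficacy.* A pilot label or doubtful planning rates lower power and precision. They do not change the type I error of a test in a randomised comparison. The one-sided 0.025 in 2.11 and the two-sided 0.05 in 2.12 also agree.
- *That no previous study can exist.* The Introduction denies only studies of the combination with lifestyle modification, and the Discussion says that adequate preliminary studies are lacking. A small earlier study without lifestyle modification fits both. What remains is that the source is uncited and its relation to the present regimen is unstated.
- *That lifestyle modification in every arm must shrink the differences.* That depends on how the effects combine. An additive background would leave the differences unchanged and synergy would widen them. The documents do not settle this.

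Dropping significance tests altogether is likewise a trade-off, and the plan need not do it.

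**Conclusion.** The point holds as an inconsistency with a measurable consequence. The claim of 80% power and the description as a small pilot cannot both describe 108 participants, and the plan's own rates agree with the pilot description. Power per comparison is about 27% to 42% at 33 per arm and 29% to 46% at 36, with 95% half-widths of about 20 to 22 points. A null result would be uninformative, and a significant one would need cautious reading as to size.

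This rests on two assumptions: that the stated rates are true, and that the primary comparison is of two proportions, herb-partitioned moxibustion against each other arm. The rates may not carry over to a regimen with lifestyle modification in every arm. The true power could then be lower or higher, and the documents do not say which.

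**What to change.** 1. **Section 2.11.** Remove or restate the claim of 80% power. Label 0.80, 0.65 and 0.60 as assumptions, cite their source, and say whether that study gave lifestyle modification to all arms. State the power (about 27% to 46% per comparison) and the 95% half-width (about 20 to 22 points) that 33 to 36 per arm provides.
2. **Section 2.12.** Make the main result the two week-4 differences in effective rate, herb-partitioned moxibustion minus heat application and minus medicated plaster, each with a 95% confidence interval. Tests at P < .05 may stay, with a statement that a non-significant result will not be read as no effect.
3. **Introduction, 2.11 and Discussion.** Use one description of the trial's status and one account of the prior evidence.

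The cost is wording and two confidence intervals, with no new data or patients. The downside is a more modest stated claim. Keeping the 80% claim instead would be far more expensive. At the stated rates and 10% withdrawal, the comparison with heat needs 138/0.9, so 154 per group (462 in total). The comparison with plaster alone needs 82/0.9, so 92 per group (276 in total).
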